### Randomization and blinding

2.5

Patients were randomly divided into one of 2 test protocols:

1.Copeptin combined with hs-cTnT group,2.cTnI group.

Randomization was performed without any stratification. Randomization listings were prepared with a probability of 1:1 and after that, randomized numbers were printed according to the results of the randomization. After the patient had given consent, the members of the inpatient clinical research center divided the patients into 2 groups according to the parity of the assigned numbers, the odd number was the test group, and the even number was the control group. Patients, doctors, inspectors, nurses and research assistants collecting data were blinded to group allocation.

### Methods

2.6

1.After admission, 5 ml cubital venous blood was collected from all patients at 0 hours, 4 hours and 6 hours, respectively. According to the digital markers assigned at admission, the blood was centrifuged at 3000 r/minutes for 10 minutes, and the plasma was collected and stored at -70°C for testing.2.cTnI detection: Immunofluorescence assay was used, the kit was produced by Roche in Germany, cTnI value <0.05ng/ml was used as the diagnostic cut-off point; (2) hs-cTnT detection: Electrochemical luminescence method was used on roche Cobas 601 automatic chemiluminescence instrument. The kit was Roche fifth generation trotropoin reagent, and hs-cTnT value ≤14 ng/L as the diagnostic cut-off point^[12]^; (3) copeptin detection: Using enzyme linked immunosorbent assay (ELISA), the kit was produced by phoenix pharmaceuticals in the United States, and the copeptin value <14 pmol/L as the diagnostic cut-off point.^[6,13]^3.All patients underwent coronary angiography as the gold standard for diagnostic validation: CAG was performed by an experienced interventional cardiologist using the standard Judkins method, with at least 3 multi-position exposures per vessel.

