## Introduction

1

Acute myocardial infarction (AMI) is an acute coronary syndrome in which blocked coronary artery causes insufficient blood supply to the heart muscle and impairs heart function, has the characteristics of rapid progression and high mortality,^[1]^ is the leading cause of cardiovascular death worldwide.^[2]^ Rapid and accurate early diagnosis of AMI is the key to reduce mortality and improve prognosis of patients.^[3]^

In the previous clinical diagnosis, AMI was mainly diagnosed based on medical history, physical examination, electrocardiogram, echocardiography and other examinations, but all of these examinations had certain defects and their accuracy was not high, while myocardial necrosis markers such as C reactive protein (CRP), myoglobin (Mb), creatine kinase isoenzyme (CK-MB) have poor sensitivity and specificity in the early stage of the disease.^[4]^ Although cardiac troponin (cTn) has become a recognized indicator for the diagnosis of AMI, the blood concentration reflecting myocardial necrosis cannot be detected within 1 hour after the onset of AMI symptoms, and the level of troponin begins to rise 3 to 6 hours after the occurrence of myocardial injury, appearing the “troponin blindness stage”,^[5]^ since cTn lacks sensitivity in the early stages of myocardial injury, it is particularly important to add a marker for rapid diagnostic AMI. Copeptin is a newly discovered marker of myocardial necrosis. Clinical studies have confirmed that copeptin begin to rise in early AMI, earlier than troponin,^[6]^ breaking the “troponin blindness stage” and making up for defects in early atypical changes in electrocardiogram. Early diagnosis and prognosis evaluation of AMI can be carried out quickly.

Some studies have pointed out that although the level of copeptin in AMI patients is significantly increased, because of the lack of specificity, it should not be considered as a single biomarker for the diagnosis of suspected AMI patients.^[7]^ The sensitivity of hypersensitive cardiac troponin (hs-cTn) is higher than that of traditional troponin. At present, the diagnostic value of hs-cTn combined with copeptin in early detection of AMI is not clear. The aim of this study is to investigate the early diagnostic value of hs-cTnT combined with copeptin in early detection of AMI.

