## Discussion

3

Since chest pain and other symptoms account for about 5% to 10% of the total number of emergency patients,^[14]^ accurate diagnosis of AMI in chest pain patients in the early stage is of great clinical value in improving the prognosis of patients and reducing their mortality.

Troponin T is a regulatory protein for myocardial tissue contraction and a biochemical marker of myocardial injury and necrosis. It is usually detected from the blood 4 to 6 hours after chest pain occurs. Traditional cTnT detection methods have lower sensitivity and affect the early diagnosis of AMI, while hs-cTnT have higher sensitivity than traditional detection methods.^[15]^ Hs-cTnT has high sensitivity to myocardial injury and strong specificity, can appear in the early stage of AMI, and can exist in the blood stream for a long period of time. It is the most favorable marker for early diagnosis and prognosis evaluation of AMI.^[16]^ The hypersensitive troponin will rise abnormally when there is damage of cardiomyocytes and the sensitivity is high, serum level of hypersensitive troponin T is positively correlated with the degree of myocardial injury in acute myocardial infarction.^[17]^

Copeptin, a part of the original C-terminal of arginine vasopressin (AVP), is positively correlated with AVP in the normal population and patients with cardiopulmonary and vascular diseases, and is an acute endogenous stress marker. Its stability in vivo is stronger than AVP, and it is easy to measure. Therefore, copeptin can replace AVP as a clinical early-warning marker of cardiovascular disease.^[18]^ The plasma copeptin level peaks immediately after AMI, and decreases gradually within 6 hours, with the largest change range within 0 to 3 hours.^[19]^ However, the copeptin specificity is low, and it can increase in acute or chronic stress state, such as respiratory tract infection, chronic obstructive pulmonary disease, heart failure, critical illness and so on, which has certain influence on the early diagnosis of AMI.^[20]^ The combination of copeptin and hs-cTnT detection is expected to improve specificity and accuracy in early diagnosis of acute myocardial infarction.

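### Section 2.6 states the marker cut-offs in the wrong direction, and nothing defines when the copeptin plus hs-cTnT test is positive

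*Protocol article*

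**What the plan says.** Section 2.6 (Methods) of the protocol article gives one cut-off per marker:

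- cTnI: "cTnI value <0.05ng/ml was used as the diagnostic cut-off point"
- hs-cTnT: "hs-cTnT value ≤14 ng/L as the diagnostic cut-off point"
- copeptin: "the copeptin value <14 pmol/L as the diagnostic cut-off point"

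Elsewhere the article says that all of these markers go up in infarction. The Introduction says "the level of troponin begins to rise 3 to 6 hours after the occurrence of myocardial injury" and, of copeptin, "although the level of copeptin in AMI patients is significantly increased". The Discussion adds: "The hypersensitive troponin will rise abnormally when there is damage of cardiomyocytes".

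The combined test is named as one of the two arms in section 2.5 but is not defined there or in section 2.6. Section 2.8 says that ROC analysis will be used to find the best cut-off and that the areas under the two curves will be compared with a Z test. It does not say what variable the curve for the combination is built on.

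The article gives two expectations for the combination. The Introduction motivates it by sensitivity: "since cTn lacks sensitivity in the early stages of myocardial injury, it is particularly important to add a marker". The Discussion expects something else: "The combination of copeptin and hs-cTnT detection is expected to improve specificity and accuracy in early diagnosis of acute myocardial infarction". Section 2.3 plans on a sensitivity of 90% in the test group and 75% in the control group.

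**The concern.** There are three linked problems.

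1. **Direction.** An inequality labelled as the diagnostic cut-off should describe a positive result. All three describe a normal one, and no sentence states which side counts as positive.
2. **Combination rule.** Two markers with one cut-off each give four possible result patterns. Two of these are discordant, and the article does not classify them. The ROC sentence in section 2.8 does not fill the gap, and it sets a data-chosen cut-off beside the fixed ones without saying which is primary.
3. **Expected gain.** More early sensitivity and more specificity are both expected from the combination, but a simple either/both rule trades one against the other relative to its components.

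The definition of the index test is at stake. If the rule and cut-off can be settled once results are known, the reported sensitivity and specificity are not those of a prespecified test. Section 2.6 is where the article sets out test positivity, so this is more than a detail that an analysis plan would routinely supply.

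**Working it through.** **The plan's own figures.** Section 2.3 uses n = 1.96² × S × (1 − S) / (L² × prevalence), with L = 0.1.

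- S = 0.90: 3.8416 × 0.09 / (0.01 × 0.8) = 43.2 (stated: 43)
- S = 0.75: 3.8416 × 0.1875 / (0.01 × 0.8) = 90.0 (stated: 90)

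Both reproduce if the 0.8 in that section is the prevalence. So 90% and 75% are the sensitivities actually used, and the planned difference is 15 points. The sample size does not depend on the combination rule.

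**Are discordant results expected?** Patients arrive within 2 hours of onset (section 2.4), so the 0-hour sample falls about 0 to 2 hours after onset. The Introduction puts the troponin rise at 3 to 6 hours. The Discussion says copeptin peaks at once and falls over 6 hours. On these kinetics a copeptin-positive, troponin-negative result at 0 hours is to be expected.

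**Bounds that hold for any dependence between the markers:**

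- Either-positive: sensitivity ≥ the larger of the two; specificity ≤ the smaller of the two.
- Both-positive: sensitivity ≤ the smaller of the two; specificity ≥ the larger of the two.

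Relative to hs-cTnT alone, either-positive cannot raise specificity and both-positive cannot raise sensitivity.

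**Size.** The article gives no single-marker accuracy, so these inputs are assumptions: hs-cTnT 75% sensitivity and 90% specificity; copeptin 60% and 70%.

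Under independence given disease status:

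| Rule | Sensitivity | Specificity |
|---|---|---|
| Either-positive | 1 − 0.25 × 0.40 = 0.90 | 0.90 × 0.70 = 0.63 |
| Both-positive | 0.75 × 0.60 = 0.45 | 1 − 0.10 × 0.30 = 0.97 |
| Difference | 45 points | 34 points |

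Without independence:

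- Let p be the probability that both markers are positive in AMI. The sensitivity difference is (0.75 + 0.60 − p) − p = 1.35 − 2p. Since p lies between 0.35 and 0.60, the difference runs from 65 down to 15 points.
- Let q be the probability that both are negative in non-AMI. The specificity difference is (0.90 + 0.70 − q) − q = 1.60 − 2q. Since q lies between 0.60 and 0.70, it runs from 40 down to 20 points.

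**Other assumed inputs, under independence.** Five sets were tried, with hs-cTnT sensitivity 75–85% and specificity 85–90%, and copeptin sensitivity 60–80% and specificity 60–70%. Either-positive sensitivity was 0.90–0.95 against 0.45–0.60 for both-positive. Specificity was 0.54–0.63 against 0.955–0.97.

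**What 90% sensitivity requires.** Under both-positive, each marker alone must reach at least 90% (about 95% each if equal and independent, √0.90 = 0.949). Under either-positive, about 68% each is enough if equal and independent (1 − √0.10 = 0.684).

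**The case against.** **The direction is a wording slip.** The thresholds are clear, the symbols read naturally as limits of normal, and the article says repeatedly that the markers rise. This stands. A reader might infer that the analysis will code low troponin as infarction and so turn the planned sensitivities into their complements. The documents do not support that, because their account of the markers supplies the intended direction. The text still needs correcting, since it labels a normal range as diagnostic.

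**The two expected gains are not strictly incompatible.** A reader might infer that the plan needs opposite rules at once. That holds only for an either/both rule judged against hs-cTnT alone. The trial's comparator is cTnI, a different assay, and against it neither rule is logically barred from raising either measure. The specificity sentence follows a remark on copeptin's low specificity, so it may mean a gain over copeptin alone. A combined score is a third option that can improve on a component in both respects, and comparing two ROC curves hints at one. All of this stands, but the article specifies no score and does not name a comparator for the gain.

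**The 90% does not prove an either-positive rule.** This is correct. Section 2.3 names no rule, and both-positive could reach 90% if each marker were sensitive enough.

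**The size rests on assumed inputs, and recruitment may leave few non-AMI patients.** Both are fair. With the strongest positive dependence, the sensitivity difference falls to 15 points, equal to the planned difference and no larger. Section 2.4 requires patients to meet AMI criteria, so the specificity figures matter only if patients without AMI are in fact enrolled.

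**Conclusion.** The point holds. As written, the cut-offs contradict the article's own description of the markers, the combined index test has no positivity rule, and the ROC-chosen cut-off neither supplies one nor is reconciled with the fixed cut-offs. The early-sensitivity rationale and the expected specificity gain cannot both follow, relative to hs-cTnT alone, from a single either-positive or both-positive rule.

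Under the assumed marker values, the open choice is worth 45 points of sensitivity and 34 of specificity with independence. The logical bounds are 15 to 65 and 20 to 40 points. At those values the sensitivity effect is never smaller than the 15-point planning difference. The sizes are illustrative; the missing rule and the reversed inequalities do not depend on them.

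**What to change.** - In section 2.6, keep the stated thresholds but write them as positive-test limits: cTnI at or above 0.05 ng/ml, hs-cTnT above 14 ng/L, copeptin at or above 14 pmol/L.
- Prespecify one combination rule for the primary analysis. Either-positive fits the rationale in the Introduction. A score is acceptable if it is fixed in advance.
- In section 2.8, make the fixed cut-offs primary and the ROC-derived cut-offs exploratory, and name the variable on which the combined curve is built.
- In the Discussion, align the expected gain with the chosen rule and state what it is relative to.

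The cost is a few operators and sentences, with no change to sample size or procedures. The real downside is that, under an either-positive rule, the expectation of better specificity than hs-cTnT alone has to be withdrawn.

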### Data collection and management

2.7

All data will be collected separately by 2 assistants, and all data will be stored and kept separately. The access to the database will be restricted to the researchers in this study team.

### Statistical analysis

2.8

SPSS 25.0 was used for statistical analysis of the data and normality test of the measurement data. The normal distribution data were expressed as $\bar{x}\pm S$, and the comparison between groups was performed by one-way ANOVA. Non-normal distribution data were represented by median and quartile, rank sum test was used for comparison between groups, Chi-Squared test was used for comparison between count data sets. Receiver operating characteristic curve (ROC) was used to screen the best diagnostic critical point value, and its sensitivity and specificity were calculated to evaluate the diagnostic effect. The area under the 2 ROC curves (AUC) was compared by *Z* test. *P* < .05 was statistically significant.

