**Methods::**

This is a prospective, randomized; double-blind diagnostic trial to investigate the diagnostic value of copeptin combined with hypersensitive troponin T detection in early acute myocardial infarction. Approved by the clinical research ethics of our hospital. Patients were randomly divided into one of 2 test protocols: (A) copeptin combined with hs-cTnT group and (B) cardiac troponin I (cTnI) group. Patients, doctors, nurses, inspectors, and data-gathering assistants were blinded to group allocation. We will focus on the sensitivity comparison of the 2 detection methods at different time periods and the sensitivity and specificity comparison of the two detection methods. Data were analyzed using the statistical software package SPSS version 25.0 (Chicago, IL).

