### Sample size

2.3

Estimation of sample contents for both test and control groups will be obtained based on anticipated sensitivity according to Buderer formula:^[9,10]^$$n=\frac{Z_{1-\frac{a}{2}}^{2}\times S_{N}\times \left(1-S_{N}\right)}{L^{2}\times Prevalence}$$

Where n = required sample size; S_N_ = anticipated sensitivity; *α* = size of the critical region (1 – α is the confidence level); Z_1-α/2_ = standard normal deviate corresponding to the specified size of the critical region (α), and L = absolute precision desired on either side (half-width of the confidence interval) of sensitivity or specificity. According to the sensitivity of the test group to be 90% and that of the control group to be 75%, the sensitivity of the control group to be 0.8, α=0.05, Z_1-α/2_ = 1.96, L = 0.1, it is calculated that at least 43 persons are required to be included on the test group and 90 persons on the control group. At last, 90 persons are selected from the test group and the control group respectively.

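### Section 2.6 fixes a cut-off for each assay, but section 2.8 computes sensitivity and specificity at a ROC-chosen cut-off in the same patients, which overstates accuracy; the plan does not say which cut-off governs

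*Protocol article*

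**What the plan says.** Section 2.6 (Methods) gives a threshold for each assay. For the control test, "cTnI value <0.05ng/ml was used as the diagnostic cut-off point". For the two markers of the test group, "hs-cTnT value ≤14 ng/L as the diagnostic cut-off point" and "the copeptin value <14 pmol/L as the diagnostic cut-off point"; these two carry literature citations.

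Section 2.8 (Statistical analysis) then describes the ROC curve as "used to screen the best diagnostic critical point value, and its sensitivity and specificity were calculated to evaluate the diagnostic effect". The next sentence adds: "The area under the 2 ROC curves (AUC) was compared by *Z* test".

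The Methods part of the abstract makes sensitivity at different times, and sensitivity and specificity of the two test schemes, the focus of the study. The article does not say whether the section 2.6 thresholds or the ROC-selected ones define a positive result in those comparisons. It gives no rule for turning copeptin and hs-cTnT into one result or one curve, and mentions no validation sample, cross-validation or optimism correction.

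**The concern.** The only sentence that says how sensitivity and specificity are obtained ties them to the ROC-selected value, not to the thresholds already fixed in section 2.6. A cut-off chosen because it performs best in a set of patients will look better in those patients than it would in new ones. Following section 2.8 as written therefore gives accuracy figures that are too high in both groups.

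Two things are at stake. First, the main results depend on which definition of a positive test is used, and with both in the text either could be reported. Second, the groups may not be inflated equally: the test group has two markers to tune and the control group has one.

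**Working it through.** **Inputs from the protocol article**
- Anticipated sensitivity 0.90 (test) and 0.75 (control), z = 1.96, L = 0.1, and a printed 0.8 (section 2.3)
- 90 patients per group (section 2.3)
- Two markers in the test group, one in the control group (section 2.5)

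**Step 1: the plan's own sample size, to find the case mix.** The formula in section 2.3 is n = z² × Sn × (1 − Sn) / (L² × prevalence).
- Test, prevalence 0.8: 3.8416 × 0.90 × 0.10 / (0.01 × 0.8) = 43.2; stated 43.
- Control, prevalence 0.8: 3.8416 × 0.75 × 0.25 / (0.01 × 0.8) = 90.04; stated 90.
- With prevalence 1.0 the results are 34.6 and 72.0, which do not match.

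So the 0.8, printed as a second control-group sensitivity, acts as the prevalence. It implies 90 × 0.8 = 72 AMI and 90 − 72 = 18 non-AMI patients per group. This is an inference, so a 45/45 mix was also run as an assumption.

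**Step 2: simulation.** There were 1,000 replicates per scenario, with independent normal markers of unit variance. The cut-off maximised J in the sample. Optimism is the apparent J minus the true J at the chosen cut-off. The two-marker group was run in two ways: an either-positive rule with both cut-offs chosen, and a fitted linear score with one cut-off chosen. In the table, d1 and d2 are the mean shifts of the first and second marker in AMI patients; the single-marker test uses d1 only.

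| AMI/non-AMI | d1, d2 | One marker | Two cut-offs | Fitted score |
|---|---|---|---|---|
| 72/18 | 1.35, 0 | 0.109 | 0.156 | 0.122 |
| 72/18 | 1.35, 0.7 | 0.105 | 0.180 | 0.120 |
| 72/18 | 2, 0 | 0.095 | 0.135 | 0.104 |
| 72/18 | 1.8, 1.0 | 0.092 | 0.161 | 0.102 |
| 45/45 | 1.35, 0 | 0.080 | 0.110 | 0.095 |
| 45/45 | 1.35, 0.7 | 0.081 | 0.131 | 0.089 |
| 45/45 | 2, 0 | 0.064 | 0.086 | 0.076 |
| 45/45 | 1.8, 1.0 | 0.070 | 0.115 | 0.075 |

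In the first row, one marker with true AUC 0.83 shows apparent sensitivity/specificity of 0.776/0.807 against true values of 0.754/0.720. Optimism is (0.776 + 0.807) − (0.754 + 0.720) = 0.109, most of it in specificity, which rests on 18 patients.

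**Step 3: difference between groups.** Subtracting the one-marker column gives extra optimism of 0.022 to 0.075 with two tuned cut-offs and 0.005 to 0.015 with a fitted score. A repeat simulation widened these slightly; the rounded ranges are 0.02–0.08 and 0.005–0.02, and for one marker 0.09–0.12 at 72/18 and 0.06–0.09 at 45/45.

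**Step 4: AUC.** A single marker's AUC involves no chosen cut-off, so it has no optimism from this source. The fitted score's apparent AUC exceeded its true AUC by about 0.005–0.01 (for example 0.834 − 0.823 = 0.011 and 0.924 − 0.919 = 0.005).

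**Step 5: with the section 2.6 cut-offs.** If these are applied unchanged, no selection takes place and this optimism is zero.

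**The case against.** **The two sections may serve different aims.** Fixed thresholds with the chi-squared test could serve the comparison at different times, and ROC the overall accuracy comparison. That is possible, and it is why the point is put as an unstated governing cut-off. It does not help the ROC part: sensitivity and specificity computed there are still optimistic.

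**A reader might infer that the plan is built to favour copeptin plus hs-cTnT.** The documents do not support that as a fact. The combination rule is not given, and section 2.8 speaks of two curves and of a best value in the singular, which fits one score per group at least as well as two tuned cut-offs. With one score the extra optimism is small. The direction held in all eight scenarios, but the size is conditional on the rule, and the imbalance disappears if the fixed thresholds define the combined test.

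**A reader might also infer that a useless second marker would come out as superior.** In the first scenario, apparent J was 0.783 + 0.810 − 1 = 0.593 with two cut-offs against 0.776 + 0.807 − 1 = 0.583 with one marker, a gap of 0.01. The standard error of a between-group difference in J, at sensitivity 0.76 and specificity 0.75, is √[2 × (0.76 × 0.24/72 + 0.75 × 0.25/18)] = 0.16. A gap of 0.01 would not by itself produce a false claim. What stands is that the loss from the useless marker (true specificity 0.681 against 0.720) is hidden.

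**The AUC test is the named ROC comparison and is largely unaffected.** This is correct, and it limits the point to sensitivity and specificity.

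**The case mix is uncertain.** Section 2.4 requires patients to meet AMI criteria, so it is unclear that any non-AMI patients will be enrolled. That is a separate problem. Without non-AMI patients, neither specificity nor a ROC curve can be calculated, so it does not rescue the ROC plan.

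**Conclusion.** The point holds in limited form. The protocol article states fixed cut-offs, then calculates accuracy at cut-offs selected in the same patients, and does not say which governs. Used as written, section 2.8 overstates one-marker Youden J by roughly 0.09–0.12 at 72/18 and by about 0.06–0.09 at 45/45. The two-marker group is probably inflated more, by a further 0.02–0.08 or only 0.005–0.02 depending on a rule that the article leaves open.

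These sizes rest on normal, independent markers with assumed separation, on selection by maximum J, on reading 0.8 as prevalence for the 72/18 mix, and on an assumed 45/45 alternative. The existence of upward bias at a cut-off selected in the same sample does not depend on those particular values. The conclusion does not extend to the single-marker AUC, and barely extends to the AUC of a fitted score.

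**What to change.** In section 2.8, state that the sensitivity and specificity comparisons use the section 2.6 cut-offs, fixed in advance. In the same place, pre-specify what makes the combined copeptin and hs-cTnT test positive; without that rule the fixed cut-offs still leave the test group's result undefined. Label any ROC-derived cut-off exploratory, and report its sensitivity and specificity only with bootstrap or cross-validated optimism correction that repeats every data-driven step, including the one that combines the two markers.

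The cost is a few lines of text, a bootstrap run, and slightly less favourable reported accuracy. No extra patients or samples are needed. The change should be made before outcome data are examined.
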